## Abstract

**Abstract:**

**Introduction:**

Learning health systems (LHS) are an approach to translate patient data into actionable clinical insights, empower healthcare teams to drive quality improvement and reduce health inequalities. Here we present a protocol for a realist evaluation to explore what works to implement a learning health system approach in primary care settings in Thailand, for whom does it work, how, why and in what circumstances.

**Methods and analysis:**

A mixed-methods realist evaluation will run in parallel with an interventional trial [Reg No: NCT06873243] in Northern Thailand which aims to improve the management of hypertension (HTN), type 2 diabetes mellitus (T2DM) and chronic kidney diseases (CKDs) using a data-supported learning health systems approach. As part of the trial, 16 primary care units (PCUs) in Chiang Mai and Lamphun provinces will be randomly selected to receive a learning health system intervention to support quality improvement for care of HTN, T2DM and CKD. Performance will be compared between intervention PCUs and all other PCUs in the region. Participants of the realist evaluation will include clinical and other professional staff involved in the development and implementation of the LHS. This realist evaluation will use both quantitative and qualitative data, including semi-structured interviews, surveys and documents from participating sites. Quantitative and qualitative findings will be systematically integrated to test, refine and validate context-mechanism-outcomes to identify consistencies, contradictions and explanatory mechanisms as part of a final programme theory for the successful implementation of the LHS.

**Ethics and dissemination:**

Ethical approval has been granted by all collaborating university Research Ethics Committees (ref: 1090, 0321, 32540). Results will be disseminated to stakeholders, including patients and the public, health providers, the Thai government and WHO office. Our methods and dissemination will be guided by National Institute for Health Research and Guidelines International Network reporting standards for Patient and Public Involvement and Engagement.

STRENGTHS AND LIMITATIONS OF THIS STUDYA key strength is that realist methodology will allow us to develop in-depth and real-world theory about the implementation of learning health systems in settings with limited integration of electronic health records.This evaluation uses mixed methods and data from a broad range of stakeholders including both clinical and non-clinical staff.A lack of focus groups may impede social consensus about potential programme theory development.The quantitative analysis relies on routinely collected data which may include recording errors and missing data.Collecting qualitative data in busy clinical settings which are relatively research naive may limit the depth to which we can identify underlying mechanisms.

## Background

### Non-communicable disease burden in Thailand

 Non-communicable diseases (NCDs) are the leading cause of death globally, accounting for most premature mortality and long-term disability.^1^ The growing burden of cardiovascular diseases (CVDs), type 2 diabetes mellitus (T2DM), chronic kidney disease (CKD) and cancers places sustained pressure on health systems, particularly in low- and middle-income countries (LMICs).^2^

In Thailand, NCDs account for 74% of all deaths and are a major contributor to premature mortality.^3^ Hypertension (HTN) and T2DM are highly prevalent and remain suboptimally controlled despite widespread service coverage under universal health coverage operated by the National Health Security Office.^4^,^6^ It is estimated that reducing the number of people living with HTN in Thailand can prevent 14 000 deaths, 27 000 strokes and 18 000 heart attacks over the next 5 years.^7^

### Non-communicable disease management in Thailand

Most NCD cases in Thailand are managed in primary care units (PCUs), which function as the frontline for the district health system.^8^ PCUs are responsible for screening, diagnosis, treatment initiation, long-term follow-up and prevention activities.^8^ Care delivery in PCUs is led by multidisciplinary teams, including nurses, public health technical officers, general practitioners (GPs) and village health volunteers.^8^ Typically, each PCU has around three to five staff and is mainly operated by nurses. Most PCUs work under district hospitals, with GPs rotating to PCUs once a month on a NCD clinic day.^9^ One PCU covers a population of approximately 10 000.^8^

While this team-based model provides strong structural foundations for chronic care management, PCUs operate as complex adaptive systems. Differences in staffing, leadership, workload, digital literacy and community context create substantial variation in how care is organised and delivered, which then affects PCU clinical performance outcomes.^9^,^13^ Furthermore, clinical audits suggest that variation in clinical performance outcomes reflects availability of healthcare resources and varying degrees of diagnostic and treatment inertia.^9^

In Thailand, electronic health record (EHR) data is used by the Ministry of Public Health to understand how whole regions deliver care.^14^ Health data from all public healthcare facilities in Thailand is uploaded to the central government via the Health Data Centre (HDC) and visualised through the HDC online dashboard.^14^ While this national system offers an overview of population health and facility performance, data is primarily collected for administrative reporting rather than local learning.^15^ Consequently, improvements in NCD outcomes are uneven across facilities, suggesting that availability of data alone is insufficient to drive quality improvement (figure 1).

**Figure 1 F1:**
[figure not shown]
Variation in HTN control across provinces in northern Thailand.^39^ HTN, hypertension.

Thailand is in the early stages of using EHRs to support quality improvement for people living with NCDs.^16^ A quality improvement (QI) intervention for HTN incorporating pop-up alerts in the EHR highlighted the importance of user-friendly decision support tools to improve ease of adoption and acceptance by healthcare workers.^17^ An ongoing study across northern Thailand is trialling the implementation of a multidisciplinary QI programme to improve screening, prevention, diagnosis and management of people with CKD.^18^ The intervention is supported by computerised decision support tools which interrogate electronic patient data to create patient lists and report summary data to healthcare teams in real time.^18^

It is recognised that NCDs co-occur in a substantive number of patients, and therefore cannot be managed in isolation. Therefore, complex systems thinking is required for the development of interventions that can tackle the burden of NCDs across the heterogenous landscape of services across Thailand. One such approach is the learning health systems (LHS) concept—guiding health systems through learning using different methods such as information, deliberation and action at different systemic levels for capacity building and health system strengthening.^19^ For example, with LHS approaches, healthcare teams can leverage EHR data to provide better healthcare and reduce inequalities.^20^

In high-income countries, LHS approaches have demonstrated benefits in chronic disease management and health system performance.^21^,^24^ However, evidence from LMICs—particularly in primary care settings—remains limited and mixed. Similar LHS interventions implemented across different settings have produced uneven outcomes, with variation in provider engagement, sustainability and impact.^15^

Existing evaluation of LHS initiatives often focuses on measurable outcomes, such as changes in clinical indicators, while paying less attention to how contextual factors influence implementation processes.^25^ Limited attention has been given to the underlying mechanisms through which healthcare providers interpret, respond to and engage with LHS components.^25^ As a result, it remains unclear why comparable interventions function differently across primary care contexts.

Thailand is structurally well-positioned to adopt LHS approaches. The country has universal health coverage, a strong district health system and a nationwide digital health information infrastructure.^26^ However, variation in organisational culture, leadership support, analytic capacity and workflow integration across PCUs suggests that the success of an LHS intervention may depend on local contextual conditions.^8 25^

Our LHS approach and trial follow on from current QI initiatives in Thailand using EHR data to embed continuous QI into routine delivery of care for NCDs, actively building an approach that eventually will help facilitate care for people with more than one NCD.^27^ This approach has been used by the Clinical Effectiveness Group (CEG) at Queen Mary, University of London, for over 25 years.

Based in north east London, CEG has implemented a clinically driven LHS in one of the most ethnically diverse and socially deprived areas of London, using locally generated data to improve the health of over 2 million people (figure 2).^28 29^ This LHS has been shown to lead to improvements in health and healthcare quality, alongside a reduction in inequalities.^30 31^

**Figure 2 F2:**
[figure not shown]
The CEG learning health system approach.^29^ CEG, Clinical Effectiveness Group; GPs, general practitioners. NHS, National Health Service

In this paper, we describe a realist evaluation to explore the individual, organisational and contextual factors and mechanisms that underpin the sustained embedding of LHS into routine delivery care for NCDs in Thailand.

### Initial programme theory

The initial programme theory (IPT) that underpins this programme has been developed based on existing evidence, experience and expert opinion of how LHSs had previously been used for NCD management in primary care in the UK and complemented by local knowledge of the Thai healthcare system. The IPT was initially drafted by the research team and then refined in a workshop with Thai stakeholders.

This IPT hypothesises how LHSs in specific contexts (C) trigger mechanisms (M) to produce outcomes (O). The initial programme theory consists of the following:

Access to more accurate, up-to-date clinical data along with training support and collaborative learning methods across organisations provides primary care staff with the knowledge and psychological tools to drive improvements in population health.Through the development of a LHS that uses these elements, staff confidence in adopting digital data-driven interventions increases and data insights allow for more targeted service planning for NCD patient populations.The combination of these contextual and mechanistic factors will eventually lead to better management of population NCD burden, along with consistent use of improvement methodology in clinical care.Using collaborative learning methods will allow for the development of peer learning networks that drive further learning and innovation in practice.

This development process for this IPT began prior to the start of the clinical outcomes trial, in Jan 2025. The clinical trial commenced in July 2025, and it is currently in the stage of piloting the LHS intervention for HTN. A draft illustration of the IPT is included in online supplemental file 1.

### Evaluation questions, objectives and focus

#### Aims

The aim of our realist evaluation is to explore the impact of the LHS approach in improving NCD management in Thailand and who it works best for, in what circumstances, how and why.

#### Objectives

The specific objectives of the evaluation are to evaluate the implementation of a LHS approach for the management of HTN, T2DM and CKD in primary care in Chiang Mai and Lamphun provinces, Thailand. Furthermore, we seek to explore whether and how LHSs impact access and use of electronic health data to improve care, and to what extent this can reduce the burden of HTN, T2DM and CKD.

####  Ethical approval

Publishing our evaluation protocol aligns with UK Medical Research Council recommendations to promote methodology development and encourage study transparency. This protocol has received ethics approval from Queen Mary University of London, London School of Hygiene and Tropical Medicine (LSHTM), and Chiang Mai University (CMU) ethics boards (ref no.: 1090, 0321, 32540).

The main outcome of the evaluation will be a refined realist programme theory. In collaboration with Thai leaders in primary care and the Thai Ministry of Public Health, we will share learning and resources from this project across Thailand and globally. The Ministry of Public Health will author a national NCD service plan based on the findings of our LHS intervention. This process will be supervised by the Division of Non-communicable Diseases. The service plan will subsequently be disseminated to regional, provincial and local healthcare teams. We will produce a paper for publication in a peer-reviewed journal and present at relevant academic conferences. We will also seek to disseminate our findings through public facing and/or professional events (eg, presenting our findings at relevant hospital trusts). Funders will have no role in the decision to publish.

#### Rationale for using realist evaluation

The LHS approach has been used internationally, with modification for differing health and care system contexts.^28^ This study will complement a LHS cluster randomised trial (RCT) and the economic evaluation that will occur in parallel. An illustration of the RCT design is included in figure 3. Random sampling has been used to allocate 16 PCUs from 419 total eligible PCUs to receive the intervention (273 units in Chiang Mai and 146 units in Lampang). This intervention is an open-label trial, as those receiving the intervention are aware of their allocation. The full details of the trial are described elsewhere.^27^ The data required for the quantitative outcomes will be collected from the EHR used in Thailand across Chiang Mai and Lamphun provinces, between 2025 and 2028, for the total population registered across the intervention PCUs for the RCT and economic evaluations.

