**Figure 3 F3:**
[figure not shown]
Thai LHS trial design. LHS, learning health system. MoPH, Ministry of Public Health

The economic evaluation will be developed from the perspective of the Thai healthcare system and use Thai unit costs. It will include costs of staff time and other resources involved in implementation and maintenance of LHS QI programme (outside PCU staff), including development and maintenance of the Active Patient link (APL) tool, staff training, facilitation visits and other QI-related activities. In addition, PCU appointments, medications, investigations, hospital attendances and admissions of patients with target conditions will be identified using EHR data and costed. The overall additional costs, including the LHS QI programme and patient healthcare, per additional patient achieving target disease management outcome with QI programme compared with usual care will be reported.

This realist evaluation will triangulate the outcomes from the trial and economic evaluation with its own data collection. We use a realist approach because it acknowledges the importance of organisational context and seeks to understand the underpinning mechanisms, rather than make one-size-fits-all judgements.

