### Strengths, limitations and future directions

Using a mixed-methods approach for this realist evaluation to complement the findings from the trial will give a rich understanding of the mechanistic and contextual factors contributing to trial outcomes. This evaluation will provide specific as well as generic learning about the adoption of data-enabled innovative tools and their use in practice for health improvement in an LMIC setting. The focus on both robust quantitative and qualitative methodology will give insight into how human and organisational factors contribute to changes in NCD management and can be sustained in practice. Other strengths of our study include previous CMU collaboration with the Thai Ministry of Public Health, LSHTM and the WHO to lead work integrating electronic patient records into care pathways for NCDs.^3 35^ CMU has access to pseudonymised patient level EHRs for all individuals residing in Lampang and Chiang Mai provinces—two of the largest provinces in northern Thailand and cover a wide range of rural and urban contexts, therefore improving generalisability of results.

Limitations include the possibility of a reporting bias or observation bias where mechanisms are partially shaped by the presence of the research team. The quantitative analysis relies on routinely collected data which may include recording errors and missing data. The qualitative analysis will identify underlying mechanisms, but is unlikely to be fully understood due to cultural factors around communication, hierarchy and external evaluation, particularly in the context of a UK-Thai research collaboration. This may limit the extent to which problems or concerns are reported by staff.

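### The EHR population stated for the RCT and economic evaluation covers the intervention PCUs and names no comparison PCUs, so neither the stated comparison nor the cost result against usual care can be computed from it

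*Protocol article*

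**What the plan says.** Under Rationale for using realist evaluation, the article describes a cluster randomised trial with a parallel economic evaluation. On allocation it states: "Random sampling has been used to allocate 16 PCUs from 419 total eligible PCUs to receive the intervention", the total being made up of "273 units in Chiang Mai and 146 units in Lampang". The closing sentence of that paragraph gives the data source. Data for the quantitative outcomes "will be collected from the EHR used in Thailand across Chiang Mai and Lamphun provinces, between 2025 and 2028", and the population is then specified: "for the total population registered across the intervention PCUs for the RCT and economic evaluations".

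Two other statements fix what those data must deliver:

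- Abstract, Methods and analysis: "Performance will be compared between intervention PCUs and all other PCUs in the region".
- Economic evaluation paragraph, following Figure 3: overall additional costs "per additional patient achieving target disease management outcome with QI programme compared with usual care will be reported". The same paragraph says that appointments, medications, investigations and hospital use will be identified from EHR data and costed.

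On access, Strengths, limitations and future directions says: "CMU has access to pseudonymised patient level EHRs for all individuals residing in Lampang and Chiang Mai provinces".

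The realist evaluation reuses the EHR sources of the other LHS studies (Study design). It looks at outcomes by site and over time to see which sites improved most and least, and gives as an example mechanism that supported use of the LHS leads to better control of hypertension (Quality improvement outcome and activity metrics).

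**The concern.** The sentence names the two analyses that depend on a comparator and assigns them a population that has none. This differs from detail left to the trial protocol: the article states a scope, and that scope does not fit the comparison and the economic result stated elsewhere in the same article.

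If the extract were built to the sentence, the trial comparison and the cost-effectiveness result would have no source for the usual-care side. The realist evaluation would inherit the gap. It aims to explore the impact of the LHS and how far it can reduce disease burden, and its findings are to inform a national NCD service plan. The article itself reports another quality improvement programme for CKD under way across northern Thailand, so change unrelated to the LHS is a real possibility. Without comparison PCUs, change common to all PCUs could be written into the programme theory as an effect of the LHS.

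**Working it through.** **Inputs, all from the protocol article**

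- Eligible PCUs: 273 in one province and 146 in the other; stated total 419 (Rationale for using realist evaluation).
- PCUs allocated to the intervention: 16 (same section).
- Stated EHR population: those registered at the intervention PCUs (same section).

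**Step 1. Reproduce the stated total.** 273 + 146 = 419, which agrees with the article.

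**Step 2. Size of the gap.** Taking the comparison PCUs to be the eligible units that were not allocated:

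- Comparison PCUs: 419 − 16 = 403, or 403/16 = 25.2 per intervention PCU.
- Share of eligible PCUs inside the stated population: 16/419 = 3.8%.
- Share outside it: 403/419 = 96.2%.

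**Step 3. Can the promised results be computed from the stated population?** Write P for the proportion of patients at target and C for mean cost per patient, with subscripts L for LHS and U for usual care.

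- Trial comparison: P_L − P_U. The stated population supplies P_L; P_U must come from the other PCUs.
- Economic result: (C_L − C_U)/(P_L − P_U). The stated population supplies two of the four terms. Patient healthcare costs within C_U also come from EHR data, so the same gap affects both numerator and denominator.

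The intervention PCUs' own baseline could be put in place of usual care, but that gives a different quantity. If e is the effect of the LHS and t the background change over the same period, the change from baseline is e + t, whereas the contrast with concurrent comparison PCUs estimates e.

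**Step 4. Does the site-level reading need comparators?** For sites i and j sharing the background change t, the difference in their changes is (e_i + t) − (e_j + t) = e_i − e_j. Ranking the sites is therefore unaffected by a common trend and can be done on intervention PCUs alone. Attributing the change at site i to the LHS is another matter: that requires e_i rather than e_i + t, and comparison PCUs supply the estimate of t. If t differs between provinces, the comparison PCUs should be from the same province.

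**Step 5. Which provinces?**

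| Place in the article | Second province |
|---|---|
| Abstract, Methods and analysis | Lamphun |
| Objectives | Lamphun |
| Rationale, data-collection sentence | Lamphun |
| Rationale, counts of eligible PCUs | Lampang |
| Strengths and limitations, EHR access | Lampang |

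The count of 403 and the statement of EHR access both belong to the Chiang Mai and Lampang version. The data-collection sentence belongs to the Chiang Mai and Lamphun version.

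**The case against.** The strongest reply is that this is loose drafting. The sentence does not say that data will come only from intervention PCUs. It names whole provinces as the source, the trial is described as a cluster RCT, all public facilities upload to the national Health Data Centre, and the university reports patient-level access for all residents of two provinces. The article is the protocol of the realist evaluation; it refers to another publication for the full trial details, and the trial design figure is not available here. All of this stands, and it makes a drafting error the likelier explanation. It does not make the sentence right: a reader who builds the extract from it would leave out the comparison group.

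Three stronger readings are tempting, and the document does not support them:

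- A reader might infer that the trial has become an uncontrolled before-after study. That treats one clause as overriding the stated comparison, the randomised design and the incremental economic result. An inconsistency does not show which statement is operative.
- A reader might infer that no reading of site improvement is valid without comparators. Step 4 shows that descriptive ranking needs none; only attribution does.
- A reader might want to put a figure on the bias from background trend. The article gives no trend, so any figure would rest on an assumption. The follow-up also differs by condition (36 months for hypertension, 24 for diabetes, 12 for CKD), so no single figure would serve.

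**Conclusion.** The concern holds as an internal contradiction in a stated data scope. The EHR population given for the RCT and economic evaluation cannot deliver the comparison in the Abstract or the cost per additional patient at target against usual care. By the article's own counts, 403 of 419 eligible PCUs (96.2%) fall outside it. That count assumes that the comparison group is the eligible PCUs not allocated to the intervention, and that the eligible total belongs to the provinces actually studied. The second assumption is open until Lamphun and Lampang are reconciled. Whether the trial itself plans to omit comparison data cannot be decided from this document. For the realist evaluation the consequence is limited to places where a site's change is credited to the LHS.

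**What to change.** 1. Reconcile the second province throughout: Lamphun in the Abstract, Objectives and data-collection sentence; Lampang in the eligible-PCU counts and the statement of EHR access. Confirm that the total of 419 and the access arrangement both apply to the provinces studied.
2. Amend the data-collection sentence under Rationale for using realist evaluation to say that EHR data for the RCT and economic evaluation are extracted for the registered populations of both the intervention PCUs and all eligible comparison PCUs (16 and 403 by the present counts, if step 1 confirms them).
3. Under Quality improvement outcome and activity metrics, keep the descriptive ranking of sites as it is. Add that where a site's change is attributed to the LHS, it will be shown beside the change over the same dates in comparison PCUs of the same province.

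The first two are corrections of wording. If the extract has in fact been limited to intervention PCUs, the second also means a wider pull of routine records. The third adds some descriptive analysis. It cannot yet be said that no further data access is needed, because the access described in the article covers Lampang and Chiang Mai and does not mention Lamphun.
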